#### Current status and impact of COVID-19 pandemic

The study protocol was approved for funding in 2017. Subject recruitment was initiated in May 2018 and had to be halted in March 2020 due to the COVID-19 pandemic. As of March 2020, neurocognitive assessments have been performed on 386 participants of the cohort out of intended 550 participants and brain MRI scans obtained on 195 participants our of intended 200. We will try to recruit more participants once the situation is conducive. We acknowledge that due to the COVID-19 pandemic there will be some reduction in the power of the study. The results will be reported as per emerging guidelines on reporting clinical studies affected by the COVID-19 pandemic.^35^

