### Subject selection

All subjects of the PMNS cohort (n=690) will be invited for participation in the study (figure 2) subject to following inclusion criteria: (1) Maternal vitamin B_12_, folate levels measured during pregnancy (2) Serial measurements done at 6, 12 and 18 years of age. Neurocognitive assessments, temperament and mental health assessments will be performed in all consenting subjects. Brain MRI will be performed on a subset of the cohort selected based on exposure to maternal vitamin B_12_ levels at 18 weeks of gestation. Median vitamin B_12_ level at 18-week gestation was 153pM (103 175 pM being the first and fourth quartiles). Description of maternal characteristics at 18-week and 28-week gestation and offspring birth characteristics are provided in online supplemental material 1. Of the 690 participants still in follow-up, 152 subjects (78 males, 74 females) whose mothers had plasma vitamin B_12_ concentration <103 pM and 154 subjects (88 males, 66 females) whose mothers had plasma vitamin B_12_ concentration >175 pM will be eligible for participation in the brain MRI scans. One hundred participants each from these two groups (total of 200 subjects) will be randomly selected.

10.1136/bmjopen-2020-046242.supp1Supplementary data

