### Statistical methods

#### Power estimation

There are 690 members of the cohort available for assessments. Assuming a 80% participation rate (from experience of previous studies on the cohort and accounting for migration) we estimate that 550 subjects would be recruited for the study. Using a test at 5% significance level, the study will have 80% power to detect an association of 0.11 SD of continuous outcome (eg, neurocognitive test score) per SD of continuous exposure (eg, maternal vitamin B_12_ level). Study of 200 subjects (100 in each group) for brain imaging will have 80% power for an effect size 0.3 and significance at p<0.05 for detecting difference between the two maternal vitamin B_12_ exposure groups.

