### Plan of data analysis

#### Objective 1

This examines the association between intrauterine nutritional exposures and neurocognitive outcomes in young adult age:

Our primary exposure of interest is maternal vitamin B_12_ and red cell folate levels. Due to lack of reliable clinical cutoffs for these micronutrients during pregnancy for our population, we prefer to use the distribution within population to classify participants. Such an approach has been used earlier to report metabolic outcomes in the offspring in this cohort.^24^ Distribution of outcome variables such as neurocognitive performance scores will be visualised by using different plotting techniques such as box plot and scatter plot. Univariate analysis (Pearson’ correlation and linear regression) will be performed to examine the relationships between the primary exposures, life course variables and neurocognitive outcomes (table 1). We expect to construct multivariate linear (if outcome is continuous) or logistic regression (categorical outcome) models to examine associations of our primary exposures with neurocognitive outcomes and extend the models to examine potential modifying and mediating effects of life course variables on the associations. Finally, we will adjust for the vitamin B_12_ intervention status (vitamin B_12_ intervention received yes or no) in the PRIYA trial. We will follow this broad scheme of analysis. Depending on observed univariate associations we may construct additional multivariate models.

Given the multitude of factors and possible collinearity, we will use dimensionality reduction techniques (such as principal component analysis or Lasso). The components might be used to construct path analytical models for exploring associations between outcomes.

#### Objective 2

This examines the association between maternal nutritional exposures and brain structural functional connectivity:

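### The pandemic pause is treated as a loss of power, but it may also leave assessment period associated with middle-versus-extreme maternal B12

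*Protocol article*

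**What the plan says.** The section on current status and COVID-19 gives the position when recruitment stopped in March 2020, against an MRI target of 200: "neurocognitive assessments have been performed on 386 participants of the cohort out of intended 550 participants and brain MRI scans obtained on 195 participants". It says that the team will try to recruit more when conditions allow, and that reporting will follow emerging guidance for studies affected by the pandemic. The consequence it names is: "We acknowledge that due to the COVID-19 pandemic there will be some reduction in the power of the study".

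Under Subject selection, "Brain MRI will be performed on a subset of the cohort selected based on exposure to maternal vitamin B_12_ levels at 18 weeks of gestation". The eligible scan groups are 152 members below 103 pM and 154 above 175 pM, with 100 to be drawn at random from each. Cognition, temperament and mental health are assessed in everyone who consents.

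For Objective 1 the authors write that "we prefer to use the distribution within population to classify participants". That section names adjustment for the PRIYA intervention, and the Objective 2 section lists imaging covariates. Neither names assessment period.

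**The concern.** The pause did not fall evenly over exposure. Scanning of the two B12 tails was 97.5% done (195/200), but the full-cohort battery only 70% done (386/550). Those seen before the pause are therefore likely to be rich in extreme B12 values, and those seen later rich in middle values.

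The outcomes include a symptom inventory, mood and anxiety diagnoses and cognitive tests, which could plausibly differ between the two periods. If they do and no period term is fitted, part of that difference would appear as a difference between B12 categories in any analysis that sets the middle against the tails, or one tail against everyone else. An association could be created or hidden, depending on the direction of the shift.

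**Working it through.** **The plan's own figures.** "There are 690 members of the cohort available for assessments", and at 80% participation 0.80 × 690 = 552, which agrees with the 550 stated. The claim of "80% power to detect an association of 0.11 SD of continuous outcome" can be checked as power = Φ(atanh(0.11)·√(n−3) − z):

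- n = 550: 0.1104 × √547 = 2.583, which gives 73% two-sided (z = 1.960) or 83% one-sided (z = 1.645). The article does not state the sidedness.
- n = 386: 0.1104 × √383 = 2.161, which gives 58% two-sided or 70% one-sided.

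So the acknowledged loss of power is real. The point below does not depend on these figures.

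**Inputs.** Cohort 690; extreme groups 152 + 154 = 306; scanned 195; assessed 386; still sought 550 − 386 = 164. If the cut-points are true quartiles, 306 is half of those with B12 measured, so the relevant cohort may be about 612. Both sizes are carried.

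**Assumptions.** (a) The 195 scanned are among the 386 and split equally between the two tails. (b) The other 386 − 195 = 191 were drawn evenly from unscanned members. (c) Later recruits are drawn evenly from those left.

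**Make-up by period.** Unscanned tail members: 306 − 195 = 111.

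- Cohort 690: tail members among the 191 = 191 × 111/495 = 42.8. Assessed: tails 237.8, middle 148.2 (38%). Left: 304, of whom 68.2 tails and 235.8 middle (78%).
- Cohort 612: 191 × 111/417 = 50.8. Assessed: tails 245.8, middle 140.2 (36%). Left: 226, of whom 60.2 tails and 165.8 middle (73%).

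**Bias without a period term** = period shift × difference in the post-pause share between the groups compared. For 690 with 164 later recruits:

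- Lowest group: assessed before 97.5 + 54.5 × 191/495 = 118.5, left 33.5, later 33.5 × 164/304 = 18.1, share 18.1/136.6 = 13.2%.
- All others: 145.9/413.4 = 35.3%.
- Middle: 127.2/275.4 = 46.2%. Both tails: 36.8/274.6 = 13.4%.

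The same steps for the other cases, with an assumed shift of 0.3 SD:

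| Cohort, later recruits | Lowest / rest, share post-pause | Bias (SD) | Middle / tails, share post-pause | Bias (SD) |
|---|---|---|---|---|
| 690, 164 | 13.2% / 35.3% | 0.066 | 46.2% / 13.4% | 0.098 |
| 612, 164 | 14.9% / 35.1% | 0.061 | 46.2% / 15.1% | 0.093 |
| 690, 50 | 4.4% / 14.3% | 0.029 | 20.7% / 4.5% | 0.049 |
| 612, 50 | 5.1% / 14.2% | 0.027 | 20.7% / 5.1% | 0.047 |

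**What is barely touched.** The two tails are depleted about equally, so the low-versus-high bias is about 0.00 SD. A simulation of the same scheme, with lognormal B12 having quartiles 103 and 175 pM, gave a bias in the linear B12 slope of −0.007 to +0.001 SD per SD at a 0.3 SD shift.

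**How far assumption (b) matters.** If all 191 unscanned assessed members came from the middle, 49% of the assessed (191/386) and 63% of those left (193/304) would be middle. With a cohort of 612 the latter is 51% (115/226). The middle-versus-tails bias at 164 recruits falls to 0.3 × (35.3% − 23.5%) = 0.035 SD, or to 0.3 × (30.4% − 29.2%) = 0.004 SD. If instead all 111 unscanned tail members had already been seen, everyone left would be middle, and the bias would be 0.3 × 164/(80 + 164) = 0.20 SD.

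**The case against.** The strongest objection is that the planned main analysis is safe. The power statement concerns a continuous exposure, and that slope is almost unbiased. The low-versus-high MRI comparison was nearly all collected before the pause, and red cell folate was not used for selection. All of this stands. A reader might infer that period is confounded with low versus high maternal B12, and so with the study's central result. The counts do not support that, because the imbalance is roughly symmetric.

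Other parts of the objection also stand:

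- No Objective 1 contrast of lowest quartile versus rest, or middle versus extremes, is fixed in the text. Classification by distribution allows such contrasts but does not require them.
- The article states neither the B12 make-up of the 386 nor that the 195 are among them. A mostly middle later intake is an inference.
- The article promises only to try to recruit more, so 164 is a maximum.
- Major depressive disorder is recorded as past or current, which dilutes any period effect on that outcome.

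A reader might also set a bias of about 0.10 SD beside the planned 0.11 SD per SD and call them equal. They are on different scales: one is a difference between categories, the other a slope per SD of exposure.

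Finally, a period covariate may sit in an analysis plan that is not shown, and the Objective 1 text calls itself a broad scheme. Its absence from the article is therefore no error in itself. What remains is that the article does describe the effect of the pause, and describes it as reduced power, when its own recruitment counts point to a second effect.

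**Conclusion.** The point holds in a limited form. The statement about power is true but incomplete. On the protocol's own counts, and assuming even drawing, about 46% of middle-B12 participants but only 13-15% of tail participants would be assessed after the pause if recruitment reached 550. Quartile, lowest-versus-rest and non-linear B12 analyses of the full-cohort outcomes could then carry a bias of about 0.03-0.10 SD per 0.3 SD of period shift.

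The size rests on three things that the documents do not give: who was assessed, who will be recruited, and whether outcomes shifted at all. With no shift there is no bias; with a different order of assessment it could be near zero or larger. This is an inexpensive safeguard to add. It does not invalidate the linear, low-versus-high or imaging comparisons.

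**What to change.** - Add an indicator for assessment before or after the March 2020 halt to the Objective 1 models.
- Prespecify a sensitivity analysis restricted to pre-pause participants for the Brief Symptom Inventory and current Mini Neuropsychiatric Interview diagnoses.
- Report the maternal B12 distribution separately for the two periods, so that readers can see whether the imbalance arose.
- In the COVID-19 section, say that comparability between exposure categories, as well as power, may be affected.

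The cost is one covariate derived from the assessment date, one degree of freedom, one extra analysis on data already held, and a sentence of text. Inviting the remaining tail and middle members at equal rates would not help: that is the even drawing assumed above, and it is what produces the imbalance.

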### Plan of data analysis

#### Objective 1

This examines the association between intrauterine nutritional exposures and neurocognitive outcomes in young adult age:

Our primary exposure of interest is maternal vitamin B_12_ and red cell folate levels. Due to lack of reliable clinical cutoffs for these micronutrients during pregnancy for our population, we prefer to use the distribution within population to classify participants. Such an approach has been used earlier to report metabolic outcomes in the offspring in this cohort.^24^ Distribution of outcome variables such as neurocognitive performance scores will be visualised by using different plotting techniques such as box plot and scatter plot. Univariate analysis (Pearson’ correlation and linear regression) will be performed to examine the relationships between the primary exposures, life course variables and neurocognitive outcomes (table 1). We expect to construct multivariate linear (if outcome is continuous) or logistic regression (categorical outcome) models to examine associations of our primary exposures with neurocognitive outcomes and extend the models to examine potential modifying and mediating effects of life course variables on the associations. Finally, we will adjust for the vitamin B_12_ intervention status (vitamin B_12_ intervention received yes or no) in the PRIYA trial. We will follow this broad scheme of analysis. Depending on observed univariate associations we may construct additional multivariate models.

Given the multitude of factors and possible collinearity, we will use dimensionality reduction techniques (such as principal component analysis or Lasso). The components might be used to construct path analytical models for exploring associations between outcomes.

#### Objective 2

This examines the association between maternal nutritional exposures and brain structural functional connectivity:

Structural brain MRI analysisVoxel-based morphometry on T1 MPRAGE anatomical images will be performed using statistical parametric mapping in Matlab. Preprocessing steps will involve coregistration, segmentation. Spatial normalisation will transform all subject data to the same stereotactic space. Grey matter images will be smoothed by convolving with an isotropic Gaussian kernel. Statistical analysis using general linear model will be used to identify regions of grey matter concentration that are significantly associated with our exposures of interest.Cortical volume, thickness and hippocampal segmentation: A surface-based morphometric technique will be employed to measure cortical volume and thickness. We will use FreeSurfer software for image analysis. Standard steps include intensity normalisation, skull stripping and removal of non-brain tissues followed by segmentation, topology correction, registration and automated parcellation. Cortical volume and thickness will be computed for 68 regions (34 in each hemisphere) using the Desikan-Kelliany Atlas. The hippocampal subfield segmentation tool in FreeSurfer will be employed to compute volumes of the various hippocampal structures as per the inbuilt atlas which defines 11 hippocampal subfield structures.Structural connectivity—diffusion tractography analysis: Diffusion-weighted images will be analysed using the ‘The Diffusion Toolbox’ software tool in the FMRIB Software Library (FSL; http://www.fmrib.ox.ac.uk/fsl/fdt/index.html). After preprocessing including motion correction and eddy current correction, the DTI indices fractional anisotropy, mean diffusivity (MD) and radial diffusivity will be computed. Structural connectome generation will be performed on the MRItrix3 software. Preprocessing steps will involve denoising and correction for eddy currents. The b0 volume of preprocessed images will be extracted and registered to the T1 image using FSL’s BET tool. The fibre orientation dispersion functions (FODs) will be generated for white matter and normalised. Probabilistic streamlines tractography will be performed by dynamically seeding the normalised white matter FOD’s. The whole brain tractogram thus generated will be used for structural connectome generation.Functional connectivity: CONN software (https://web.conn-toolbox.org/) will be used for the analysis of rsfMRI data. This will involve standard preprocessing steps such as realignment, normalisation to MNI space, elimination of temporal linear trends and regressing out nuisance covariates such as residual motion and physiological artefacts. aCompCor will be used for minimising physiological artefacts. Motion censoring and interpolation will also be used to remove the effects of large frame wise displacements due to head motion. Following preprocessing, mean time series will be extracted from 91 cortical and 15 subcortical regions in the FSL Harvard-Oxford atlas, as well as from 26 cerebellar regions in the AAL atlas. These time series will be used in a whole brain functional connectivity analysis employing Pearson’s correlation coefficient between the mean time series.

For each modality, the following statistical comparisons will be performed. We will first perform correlations between maternal vitamin B_12_ and folate exposures with brain MRI outcomes to examine for any linear relationships. We will use an analysis of covariance model to examine differences in MRI outcomes between low and high maternal vitamin B_12_ groups. Similarly, we will examine for differences between low and high maternal red cell folate groups (selected based on median value of maternal red cell folate) and for any interaction between maternal vitamin B_12_ and folate status. Variance due to subjects’ age, gender, total intracranial volume, ACEs will be regressed out of the analyses. Effects of additional factors (such as current vitamin B_12_ status of offspring, education status, socioeconomic status) will be examined.

For making inferences from multimodal imaging data, we will adopt a hierarchical approach. Accordingly, we will perform voxel-wise tests for difference in grey matter volume (or cortical thickness). For brain regions which are significant, DTI-based structural connectivity and fMRI-based functional connectivity between those regions will be investigated. This strategy assures that the effects of interest have both structural and functional aetiologies, and hence are likely to be robust and reproducible.

#### Objective 3

This examines causality of association between maternal nutritional factors and neurocognitive outcomes. The genetic determinants of vitamin B_12_ have been described in our population using GWAS,^36^ which will be used to calculate a gene risk score of vitamin B_12_ deficiency. Mendelian randomisation analysis (triangulation and instrumental variable analysis) using the genetic risk score for vitamin B_12_ deficiency and homocysteine (MTHFRrs1801133) will be performed.

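### Imaging analysis: red cell folate is median-split without need, and B12 correlations from a two-tail sample overstate the cohort correlation

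*Protocol article*

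**What the plan says.** All references are to the protocol article.

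- **Subject selection.** The scanned subset is chosen on one exposure: "Brain MRI will be performed on a subset of the cohort selected based on exposure to maternal vitamin" B12 at 18 weeks. Offspring are eligible if maternal B12 was below 103 pM (152 people) or above 175 pM (154 people), out of 690 in follow-up. One hundred are drawn from each side.
- **Plan of data analysis, Objective 2, first step.** "We will first perform correlations between maternal vitamin B_12_ and folate exposures with brain MRI outcomes to examine for any linear relationships". No allowance for the two-tail sampling is mentioned.
- **Objective 2, second step.** An "analysis of covariance model to examine differences in MRI outcomes between low and high maternal vitamin B_12_ groups".
- **Objective 2, third step.** A like comparison of folate groups, "selected based on median value of maternal red cell folate", and a test of interaction between B12 and folate status. Because the interaction follows directly on the two folate groups, its natural reading is a 2x2 test.
- **Current status and impact of COVID-19 pandemic.** 195 of the 200 intended scans had been obtained by March 2020.

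**The concern.** There are two separate problems, one for each exposure.

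**Folate.** Grouping B12 follows from the sampling, because only the tails were scanned. Folate was not sampled on, so its full range is available, and cutting it at the median discards differences within each half. The study hypothesis is a pattern of lower B12 with higher folate and homocysteine, so the B12-folate interaction bears directly on it. In imaging, the only continuous step described for folate is a correlation; no continuous interaction is described. The article already concedes some loss of power from the pandemic, and this further loss is avoidable.

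**B12.** A correlation coefficient depends on the spread of the exposure. Removing the middle of the B12 distribution widens that spread, so r in the scanned sample is larger than r in the cohort even when the relation is the same. Taken at face value, the imaging correlations would look stronger than the cohort relation. They could not be set beside the full-cohort correlations planned under Objective 1.

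**Working it through.** **The plan's own figures.** The article gives no figure for the folate split, the interaction or the imaging correlations. Its imaging power statement (100 per group, effect size 0.3, 80% power) concerns the B12 group contrast only. Read as a standardised mean difference at two-sided 5%, it is not reproduced: the detectable difference is 2.80 x sqrt(2/100) = 0.40 SD. That is a separate matter, and nothing below depends on it.

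**Folate split.** Assumptions: folate roughly normal, effect linear, outcome SD 1, two-sided 5%, 80% power (multiplier 2.8016).

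- Efficiency of a median split against the continuous variable: 2/pi = 0.637, a loss of 36%.
- Effective scans for folate: 195 x 0.637 = 124; 200 x 0.637 = 127.
- 2x2 interaction, 200 scans, 50 per cell: 2.8016 x 4/sqrt(200) = 0.79 SD for the difference of differences.
- Continuous folate by B12 group: detectable slope difference 2.8016 x 2/sqrt(200) = 0.396 per SD of folate. The means of the two halves of a normal variable lie 1.596 SD apart, so on the 2x2 scale this is 0.396 x 1.596 = 0.63 SD.
- Ratio: 0.79/0.63 = 1.25, which equals 1/sqrt(0.637).

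**B12 correlation in the two tails.** Assumption: normal exposure. For tail share p, let c = z(1-p). The variance ratio is v = 1 + c x phi(c)/p, and r in the sample is r x sqrt(v)/sqrt(1 + r^2(v-1)).

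- Exact quartile tails, p = 0.25: v = 1.857, SD ratio 1.36.
- The article's counts, 152/690 = 22.0% and 154/690 = 22.3%; taking p = 0.22: v = 2.039, SD ratio 1.43.

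| Cohort r | r with 25% tails | Inflation | r with 22% tails | Inflation |
|---|---|---|---|---|
| 0.10 | 0.136 | 36% | 0.142 | 42% |
| 0.20 | 0.268 | 34% | 0.280 | 40% |
| 0.30 | 0.394 | 31% | 0.410 | 37% |

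For a log-normal exposure analysed on the raw scale with quartile tails, the SD ratio is 1.35 to 1.36 (log SD 0.6 down to 0.3).

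**What is not affected** (simulation, quartile tails).

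- B12 slope: 0.150 in the full population and 0.150 in the tails.
- Type I error of the correlation test with 200 scans: 4.6% against a nominal 5%.
- Folate correlations in the B12-selected sample: inflation about 0%, 2% and 6% for assumed B12-folate correlations of 0, 0.2 and 0.4.

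**Cost of grouping B12.** Let m = phi(c)/p be the mean of a tail. Two-group against continuous analysis of the same scans has efficiency m^2/v = 0.87 (25% tails) or 0.89 (22% tails), a loss of 11 to 13%. Against 200 randomly chosen scans analysed continuously, the two-tail contrast carries m^2 = 1.62 times the information with quartile tails.

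**The case against.** The strongest reply is that the plan does not rely on grouping alone. It begins with continuous correlations for both exposures, and Objective 1 plans Pearson correlation and linear regression. The correlations are a first look, no sentence offers them as cohort effect sizes, and the tests keep their level. This largely stands. The loss is confined to the folate group comparison and the interaction, and the inflation concerns the reported size of r, not the validity of inference.

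It is also fair that the figures rest on assumed distributions. The article's B12 values fit neither a normal nor a log-normal shape well: the median is 153 pM, whereas quartiles of 103 and 175 imply 139 (arithmetic midpoint) or sqrt(103 x 175) = 134 (geometric). The number of the 690 with measured B12 is not given, and the text shown gives no folate distribution. Hence the ranges.

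That coding belongs in an analysis plan does not answer the imaging point, because there the median split is stated outright.

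Four stronger readings are tempting but not supported:

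- **That the whole plan discards a third of its information, or that both percentages apply to both exposures.** The 36% loss belongs to the folate split. Grouping B12 costs 11 to 13%, and sampling the tails itself adds information. The 36 to 42% inflation belongs to B12.
- **That Objective 1 suffers the same loss.** There the authors write "we prefer to use the distribution within population to classify participants", but name no cut-point, and regression is planned alongside. The power statement "per SD of continuous exposure" is compatible with those analyses.
- **That the split harms the interaction most.** The proportional loss is the same 1.25 for main effect and interaction. The interaction is hard to detect mainly because it is an interaction in 200 scans; even with continuous folate it needs 0.63 SD.
- **That inflated correlations produce false positives.** The simulated error rate shows otherwise.

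**Conclusion.** The point holds for the imaging analysis only. It is a matter of efficiency and reporting, not of invalid inference.

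- The median split of red cell folate is a stated choice that the sampling does not require. Under rough normality and linearity it gives up about 36% of the folate information and raises the detectable interaction by a factor of 1.25. The 0.79 SD figure also assumes equal cells and reads the interaction as 2x2.
- Raw B12 correlations from the scanned sample overstate the cohort correlation by 36 to 42% at small r under a normal exposure, and by less at larger r. The upper figure takes 690 as the denominator for the tails.

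**What to change.** In the imaging section:

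1. Keep the low/high B12 contrast, since the sampling was built on it.
2. Replace the folate median split with red cell folate as a continuous term, log-transformed if skewed, together with its product with B12. Add a spline check for curvature. Folate categories can remain in descriptive tables.
3. Report B12 associations as covariate-adjusted slopes per cohort SD of B12. If correlations are wanted, correct them for range with r = r'/sqrt(v - r'^2(v-1)), where r' is the observed correlation and v is the ratio of the B12 variance in the scanned sample to that in the cohort. Label any raw correlation as coming from a two-tail sample.

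The cost is wording only: no new data, visits or scans. The small downside is a linearity assumption, which the spline checks for folate. For B12, linearity between 103 and 175 pM cannot be checked in the scans, because nobody in that range is eligible for scanning; the report should say so.
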